**Figure 1 figure1:**
[figure not shown]
Process flow for choosing a promising innovation. CQMF: Quebec College of Family Physicians.

#### Support for Scaling

The steering committee will establish a support network for the innovation team. Supporting organizations will be instructed to offer support and advice for scaling without providing a ready-made scaling plan. We will conduct semistructured interviews and focus groups, with the following four categories of interviewees: (1) decision makers from health and social care organizations (n=1-4), (2) health care providers (n=3-8), (3) members of the innovation team responsible for scaling (n=2), and (4) end users (n=2-4).

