**Objective:**

We aim to observe, document, and analyze how, in real-life conditions, 1 primary care innovation spontaneously scales up across Quebec, Canada.

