Most scaling occurs in the absence of scaling guidelines [5]. While there are attempts to establish rigorous and standardized guidelines, there is also a pressing need for studies that look at how scaling currently occurs on the ground when a promising or effective health care innovation is naturally or “spontaneously” expanded to reach a broader population. We adopted ExpandNet’s definition of spontaneous scaling as “diffusion of the innovation without deliberate guidance” [18]. The likelihood of spontaneous scaling is highest when the innovation effectively meets a clearly recognized need in a population or when a significant and urgent harmful event brings attention to the need to scale, for example, the COVID-19 pandemic [18]. Although the effectiveness of the innovation to be scaled should be demonstrated by its positive impacts on the public good, that is, it improves the well-being of individuals and populations through an increase in the quality of care [5,8], many experts and decision makers recognize that this is not always possible when facing a public health emergency [15,19]. Observation and analysis of spontaneous scaling are necessary to capture this process of adjusting plans and practice in real-life situations and will inform the knowledge base of scaling. Therefore, we aimed to observe, document, and analyze the spontaneous scaling (ie, that reflects the needs of a population but does not follow guidelines) of a promising primary care innovation within a specific health care context, compare it with the guiding principles of scaling described by McLean and Gargani [7-9], and make recommendations.

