### Coproduction Approach and Project Governance

Following the integrated knowledge translation approach [26,27], this study embraces the active engagement of knowledge users as equal partners working alongside researchers in all research steps. Through coproduction [28,29], we aim to generate knowledge that is valuable and meaningful to all stakeholders involved in the research process.

To ensure effective project governance, the research team will establish a steering committee consisting of key stakeholders who will provide expert advice, recommendations, and feedback on questions as they arise. This committee will oversee and coordinate each stage of the study and focus on topics that directly impact the project. The committee members will include the project leader; study coordinator; coinvestigators (1 or 2); knowledge users (1 or 2); and end users, who may include citizen or patient partners (1 or 2). This diversity of stakeholders ensures inclusive representation throughout the project’s duration.

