### Participants

#### Criteria for Choice of Innovation, Innovation Team, and Target Site

We will choose an innovation from a previous edition of the *Innovation Symposium*, a program organized by the Quebec College of Family Physicians inspired by the TV program “The Dragon’s Den” [30]. This event allows innovators, most of whom are from a clinical context and not from a research background, to pitch their promising innovations to clinical leaders and influential stakeholders (the Dragons) in Canada’s primary care ecosystem. If the Dragons consider the innovation promising, they will contribute toward accelerating its growth and scaling it. Based on our research team’s firsthand experience as attendees at previous symposiums (2017, 2019, and 2022), we will identify a spontaneous primary care innovation with considerable potential for scaling.

We will determine if the team is willing to participate in the project and, through a three-part questionnaire, whether (1) the innovation, (2) the innovation team, and (3) the context in which the innovation is embedded meet the following inclusion criteria based on our previous work [31-33] (Figure 1).

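### The study arranges scaling advice for the team it observes, while defining its subject as scaling without deliberate guidance, and the analysis does not mark which actions followed that advice

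*Protocol article*

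**What the plan says.** The Abstract's Objective reads: "We aim to observe, document, and analyze how, in real-life conditions, 1 primary care innovation spontaneously scales up across Quebec, Canada". The Introduction adopts a definition of spontaneous scaling as "diffusion of the innovation without deliberate guidance", and the Abstract's Background explains the term in the same sense. Later in the same Introduction paragraph, where the aim is stated, the term is glossed differently, as scaling "that reflects the needs of a population but does not follow guidelines".

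Under Support for Scaling the article says: "The steering committee will establish a support network for the innovation team". It continues: "Supporting organizations will be instructed to offer support and advice for scaling without providing a ready-made scaling plan". Under Coproduction Approach and Project Governance, "the research team will establish a steering committee consisting of key stakeholders", and its members include the project leader, the study coordinator and one or two coinvestigators.

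The Data Analysis section sets two tasks. The first is to compare the team's scaling plan with what was implemented at the target site. The second is to find where participants' experience agrees or disagrees with the four guiding principles: justification, optimal scale, coordination and dynamic evaluation.

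**The concern.** The object of study is defined by the absence of deliberate guidance, yet a body set up by the research team arranges guidance for the team under observation. If the team changes its plan or its implementation after receiving that advice, the analysis as described would count the change as part of the spontaneous process.

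Both analytic tasks are exposed. The plan-versus-implementation comparison can shift because either side may change after advice. The judgement on the four principles can shift because an observed agreement or disagreement may owe something to the support. Conclusions about how scaling proceeds unguided would then rest in part on guided actions, and a reader of the results could not tell which.

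**Working it through.** No arithmetic applies. This is a descriptive qualitative single-case study with no hypothesis test, and the article gives no figure that bears on the point. The check is a comparison of the text in five steps.

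1. **Definition against action.** The adopted definition excludes deliberate guidance. The support section provides for organizations that are instructed to advise on scaling. Advice that is arranged and instructed is deliberate. The only stated limit is that no finished plan is supplied, which restricts the form of the guidance and leaves advice in place.

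2. **Whose action it is.** The steering committee sets up the network. The research team sets up the committee, and the project leader, coordinator and coinvestigators sit on it. The support is therefore arranged by the study and is not something the study merely came across. Elsewhere, under Target Site, the researchers describe themselves as nonparticipant observers in the team's meetings.

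3. **Which result is touched.** The Scaling Framework section describes coordination as connecting the various actors in scaling, and it lists enablers among them. A network of supporting organizations built for the team supplies links of that kind, so the coordination finding is the most directly exposed. Advice could also reach justification, optimal scale and dynamic evaluation, but the text gives no comparably direct link for those three.

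4. **Whether the analysis separates it.** The Data Analysis section codes material against the principles and seeks consensus between coders. It does not treat support as something to be coded. The four interview topics listed for the innovation team cover the innovation, opinions on scaling, the plan, and experience of making and carrying out the plan; support received is not named. Triangulation, participants' checking of summaries, description of context and circulation of the report can confirm that events are recorded accurately. They do not by themselves show whether an action followed study-arranged advice.

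5. **What data could separate it.** The planned sources are weekly emails and monthly meetings for 1 year, observation notes from key meetings, minutes, email exchanges and monitoring data. These could capture support contacts with little added effort. What is lacking is an instruction to record and code them.

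**The case against.** The strongest reply is that the aim is stated with the looser gloss. Scaling that does not follow guidelines can tolerate advice, and the bar on a finished plan then looks like a deliberate safeguard. This has force: it shows that the authors thought about the boundary. But the definition they say they adopted is the stricter one, and the two wordings give different answers on whether the support is compatible with the object of study. That needs resolving in the text.

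A second reply is that the study is participative. The governance section justifies partnership in the research steps; it does not explain supplying scaling support to the observed team. A third is that an article may leave codebook detail to a full protocol. That is fair for the detail of coding, but the conflict between definition and action is in the printed text.

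Four stronger readings might be inferred, and the documents do not support them:

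- **That the results will be biased toward agreement with the principles.** This is plausible, but nothing says that the supporting organizations know or promote the principles, and their advice could equally diverge from them.
- **That the main question cannot be answered.** The inclusion criteria require spontaneous demand, a completed pilot and the team's own scaling governance, so some activity is likely to precede the network.
- **That the symposium programme also contaminates the case.** The article says of its judges that, for innovations they find promising, "they will contribute toward accelerating its growth and scaling it". That help comes from outside the study and belongs to the real-life context being observed.
- **That the improved scaling plan promised under Knowledge Mobilization intrudes on the observation year.** It is to be based on the results, and nothing places its delivery within that year.

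**Conclusion.** The contradiction stands on the printed text. The study defines its subject as unguided scaling, arranges guidance for the team it observes, and describes no way of telling supported actions from the rest. Findings on the four principles, coordination first, may partly reflect study-arranged support.

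The size and direction of the effect cannot be derived. Both depend on when the support starts, how often it is given and what is advised, and none of these is stated. The range runs from negligible, if the network is hardly used, to most planning and implementation steps in the observation year, if it is active from the start. The conclusion assumes that the stricter definition governs, as the article says it does. If the looser gloss governs, the definitional conflict eases, but the need to show what followed the support remains.

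**What to change.** 1. Reconcile the Introduction's definition, including its looser gloss, with the Support for Scaling section, and state which meaning of spontaneous governs the conclusions.
2. Record each study-arranged support contact (date, source, advice given) through the weekly emails, monthly meetings, observation notes and documents already planned.
3. Add one code to the template that marks each change in plan or implementation as preceding or unrelated to support, following support, or unclear. The third category matters, because attribution will not always be possible in an interpretative case study.
4. Report concordance with each of the four principles with this distinction visible.
5. Describe the case as spontaneously demanded but externally supported, and limit conclusions about unguided scaling accordingly.

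The cost is one log, one extra code on material already being collected, and a narrower claim. The article reports that data collection began in December 2023, so any contacts before the log starts would have to be reconstructed from emails and minutes. Two more drastic options are to defer the network until observation ends or to base conclusions only on unprompted actions. Both are debatable trade-offs and are not needed to resolve the point.

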### Recruitment

The innovation team will be asked to appoint a coordinator who will act as the primary point of contact between the research team and the innovation team. This individual will serve as a facilitator and work closely with decision makers, health care providers, end users, and the research team to ensure effective communication and collaboration. Additionally, the coordinator will be responsible for identifying potential participants and providing their names to the research team for consideration for semistructured interviews and focus groups. Once potential participants have been identified, the research team will send them an email inviting them to participate in the study. The email will outline the main objectives of the research and extend an invitation to participate.

### Qualitative Data Collection

#### Innovation Team

We plan to ask the team about (1) the components of the innovation (including technical requirements and costs) and its impacts on patients and health care professionals, (2) their opinions on how and why it should be scaled, (3) their scaling plan and strategies, and (4) their experiences of creating and implementing the scaling plan. We will also document any challenges encountered and how they were addressed in practice. We will follow developments with weekly emails and monthly follow-up meetings for 1 year.

#### Target Site

We intend to seek input from a range of decision makers (n=1-4), health care professionals (n=3-8), and end users (n=2-4) at the target site, as identified by the innovation team, regarding their firsthand experience with implementing the scaled innovation. We will conduct 1-hour semistructured interviews and focus groups (n=6-8). Participants in both interviews and focus groups will be asked about the innovation and their experience of scaling the health innovation, their view on the successful adaptation or not of the innovation, suggestions for improvement, potential factors influencing its implementation in their context, and possible complementary actions to be put into practice. One-hour individual structured interviews will be conducted face-to-face or on digital platforms (Teams [Microsoft Corp] or Zoom [Zoom Technologies Inc]) and adapted to accommodate the availability of participants. We will hold focus groups with the health care providers lasting 2 hours (maximum) outside office hours to reduce the impact on the services offered. Interviews will be conducted in English or French. One of the research team members with expertise in scaling and training in health care research innovation will conduct the interviews and focus groups. The interviews and focus groups will be recorded and transcribed, while an assistant moderator will be responsible for taking meeting notes during the interviews and focus group sessions. We will also participate as nonparticipant observers in some key meetings of the innovation team or training sessions given by the innovation team. During the observation periods, the research team will take observation notes about the meeting and the scaling process.

### Interview Guide

The interview guide will be based on the 4 McLean and Gargani guiding principles of scaling and will be adapted to the different roles of the interested parties (1 interview guide for decision makers, health professionals, and the innovation team and another one for end users).

We plan to carry out supplementary descriptive quantitative data collection that includes self-administered questionnaires to collect sociodemographic information from each participant (eg, age, sex, gender, civil status, and employment status) involved in the semistructured interviews in addition to a descriptive data collection of organizational characteristics of the target scaling site. The second source of quantitative data will be the various documents describing the scaling process (eg, archival records, reports on the innovation development, minutes of meetings, email exchanges, data from the monitoring of scaling, training manuals and materials, and postintervention feedback) to complement and support our qualitative analysis [34]. We will proceed to content analysis and direct analysis based on the 4 McLean and Gargani guiding principles, providing a comprehensive account of the execution of the scaling plan for detailed analysis.

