**Methods:**

We will conduct a participative study using a descriptive single-case study. It will be guided by the McLean and Gargani principles for scaling and reported according to the COREQ (Consolidated Criteria for Reporting Qualitative Research) guidelines. Informed by an integrated knowledge translation approach, our steering committee will include patient users throughout the project. Inspired by the Quebec College of Family Physician’s “Dragons’ Den” primary care program, we will identify a promising primary care innovation that is being or will be scaled spontaneously. We will interview the innovation team about their scaling experiences every month for 1 year. We will conduct interviews and focus groups with decision makers, health care providers, and end users in the innovation team and the target site about their experience of both scaling and receiving the scaled innovation and document meetings as nonparticipant observers. Interview transcripts and documentary data will be analyzed to (1) compare the spontaneous scaling plan and implementation with the McLean and Gargani principles for scaling and (2) determine how it was consistent with or diverged from the 4 McLean and Gargani guiding principles: justification, optimal scale, coordination, and dynamic evaluation.

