Inclusion criteria for the innovation: there is a spontaneous demand for scaling, the innovation aims to meet a demand for relevant primary care and services in the province of Quebec, the innovation has an epidemiological justification, the innovation is part of a health organization in Quebec, and the innovation has already been piloted and shown to be effective.Inclusion criteria for the innovation team: it has a committee or governance for the development and scaling of the innovation, it is part of a health organization in Quebec, it accepts that the research team participate as an observer in its strategic meetings, it agrees to nominate a person to be the coordinator responsible for the monthly and weekly follow-up with the members of the research team, the innovation team coordinator accepts the responsibility for connecting the research team with managers and health professionals in the target scaling setting, and the innovation team will be available during the research period (1 year) for monthly update meetings to respond to weekly ad hoc email requests from the research team on the innovation and the scaling process.Inclusion criteria for the target site: a specific geographical place is targeted to receive the innovation or there are professionals already using the innovation in the place where it is exposed who are not members of the innovation team, the plan for receiving the scaled innovation is embedded in a health organization in Quebec, an organizational structure is available for receiving the scaled innovation, and partners in the target site are in place to support the scaling plan.Inclusion criteria for individual participants: participants must be at least 18 years old; able to provide informed consent; able to actively participate, read, understand, and communicate in English or French; involved; in contact with or affected by the scaling initiative; and a decision maker in a health and social care organization, a health care provider, or a scaling expert working in the province of Quebec.

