### Knowledge Mobilization

Our knowledge mobilization plan is to involve knowledge users (eg, investigators, health care providers, and decision makers) and end users (eg, patient partners) in the steering committee. They will meet every 3 months via teleconference to discuss research progress and provide guidance on research directions. Our team already has extensive experience in the involvement of end users in the design, development, and implementation of health care solutions. Our approach considers the opinions of all end users as equally important. We will send out a newsletter every 4 months for all stakeholders.

We will produce and deliver an adapted and improved scaling plan, based on our results as seen through the lens of the McLean and Gargani guiding principles, to the innovation team. An executive report will be made available free of charge on the research team’s website. We will prepare summaries of our research results tailored to specific knowledge user groups such as clinicians’ organizations (family physicians, nurses, psychologists, and social workers) and researchers (peer-review publications).

Finally, we will disseminate study results in the form of (1) recommendations for preparing and monitoring scaling in primary care with an ethical lens, (2) presentations at scientific and professional conferences, (3) publications in peer-reviewed journals, and (4) through relevant networks such as the Research on Patient-Oriented Scaling-up network, the Strategy for Patient-Oriented Research (SPOR) Evidence Alliance, the Quebec College of Family Physicians and Réseau-1 Québec.

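### The innovation team's interview guide, the codes and the yardstick all come from the same four principles, and the analysis does not separate evidence from before and after the team meets the guide

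*Protocol article*

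**What the plan says.** The Introduction of the protocol article defines spontaneous scaling as "diffusion of the innovation without deliberate guidance".

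Under Interview Guide, "The interview guide will be based on the 4 McLean and Gargani guiding principles of scaling", with "1 interview guide for decision makers, health professionals, and the innovation team and another one for end users". The innovation team is therefore an intended recipient of a principle-based guide. Under Support for Scaling, two members of that team are to be interviewed.

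The contact schedule is described in three ways:
- Abstract, Methods: "We will interview the innovation team about their scaling experiences every month for 1 year".
- Qualitative Data Collection, Innovation Team: "We will follow developments with weekly emails and monthly follow-up meetings for 1 year". The topics listed there are the components and impacts of the innovation, views on how and why to scale it, the plan and strategies, and experience of making and carrying out the plan. Challenges are also documented.
- Inclusion criteria for the innovation team: availability for "monthly update meetings to respond to weekly ad hoc email requests from the research team on the innovation and the scaling process".

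Under Data Analysis, Theoretical Model, codes are drawn up in advance from the four principles. The analysis compares the plan with its implementation and judges where participants' accounts agree or disagree with those principles. Under Validation, the safeguards are triangulation across sources, a description of context, and circulation of the report. Participants are also sent summaries of their interviews to check.

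**The concern.** One framework fills three roles: it shapes the questions, it supplies the codes, and it is the standard of judgement. That is normal in framework analysis when the people questioned only report on a process. Here the people questioned also control it. A question about why the innovation should be scaled, or how it is being evaluated, can prompt a team to add a rationale or an evaluation step that it would not otherwise have had. That step would then be coded as agreement with the principle.

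The central question is how far scaling without deliberate guidance agrees with or departs from the four principles. If the study's own questions move the team toward the principles, part of the observed agreement comes from the study and not from spontaneous scaling. This route is separate from the support network, because it would exist even without that network.

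**Working it through.** The article states no sample size calculation, error rate or effect size that bears on this point, so the check sets the statements side by side.

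**1. Is the instrument the same as the yardstick?** Yes. Interview Guide and Theoretical Model both name the four McLean and Gargani principles, the first for the questions and the second for the codes and the concordance judgement.

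**2. Does the team being judged receive the instrument?** Yes. Interview Guide lists the innovation team among the recipients of the first of the two guides.

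**3. Is the process still open to change while the team is questioned?** Yes. The Innovation Team section follows the making and carrying out of the plan over the year, including how challenges were handled. Scaling Framework treats adaptation of plans as expected.

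**4. How much contact is there?**
- Monthly contacts: 1 per month × 12 months = 12.
- Weekly emails: 1 per week × about 52 weeks = about 52.
- Total: 12 + 52 = about 64 scheduled contacts in the year.

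This counts contacts. It does not count exposures to the principles.

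**5. Which contacts use the principle-based guide?** The article does not say. The abstract calls the monthly contacts interviews, which could link them to the guide. The Innovation Team section and the inclusion criteria call them follow-up or update meetings, which suggests a separate and lighter instrument. The guide could belong only to the semistructured interviews under Support for Scaling. The article gives no time for the first guided interview, so the number of exposed contacts is unknown.

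**6. Would the milder reading remove the risk?** No. A single early guided interview could carry over into later planning. Some of the listed topics also lie close to a principle: Scaling Framework explains justification through why or whether to scale, technical feasibility and impact, and the Innovation Team section asks about technical requirements, impacts, and how and why to scale.

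**7. Do the stated safeguards separate prompted from unprompted agreement?** No. Triangulation checks whether sources agree. Minutes, emails and observation notes made after the team met the guide come from the same exposed team, so they can agree with its interviews for the same reason. Context description, member checking and circulation of the report test accuracy, not the origin of the behaviour.

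**8. Is there less exposed evidence?** Probably. Interview Guide lists archival records and development reports, some of which may predate contact. Target-site participants are not described as questioned monthly. The stated analysis does not keep these sources apart from the rest.

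**The case against.** The strongest reply is that the article never assigns the principle-based guide to the monthly contacts. The Innovation Team section has its own open topics, not set out as the four principles, and two other descriptions call these contacts meetings. A reader might infer that nearly every monthly data point after the first comes from a team already taught the principles. The documents do not support that: it requires the guide to be used in month 1, which is stated nowhere. The guide's wording is not shown, and a guide based on a framework need not disclose it.

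A reader might also infer that the newsletters feed the principles back to the team ("We will send out a newsletter every 4 months for all stakeholders", so 12 / 4 = 3 in the year at most). Their content is not stated, so this cannot be counted as exposure. Nor is there a basis for saying that some principles are affected more than others. For justification in particular, the selection criteria already require spontaneous demand, an epidemiological rationale and piloting with shown effectiveness, so part of that evidence precedes any interview.

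It is also fair to say that moving all principle-based questions to month 12 would rely on year-long recall, and that resting conclusions only on unprompted material would set aside a main source of a participative study. Both are debatable trade-offs, and neither is needed.

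Finally, an article may leave to the full protocol which script is used at which contact. That limits any complaint about missing detail. It does not answer the point about what is stated: guide basis, recipients, repeated contact and yardstick coincide, and the stated analysis draws no line at first exposure.

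**Conclusion.** The concern holds as a risk of measurement reactivity. The innovation team receives questions built on the standard by which its scaling will be judged, is contacted repeatedly while the plan can still change, and is studied as an example of unguided scaling. The likely direction of bias is toward concordance. Its size is unknown and cannot be derived from the article; the roughly 64 contacts show opportunity, not dose.

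The conclusion assumes that the guide is used with the team at some point before its plan and practice are final, and that its questions reveal at least part of the principles. A reader might go further and conclude that the study does teach the team the principles, or that none of its concordance evidence can be trusted. The documents support neither: the guide is not shown, and archival documents and target-site accounts are less exposed. The change is worth making because it concerns the central question and costs little.

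**What to change.** 1. Record the date on which the team first meets the principle-based guide. Secure its scaling plan and related documents as they stood before that date.
2. State which instrument is used at the monthly contacts. Keep monthly and weekly follow-ups to the open topics of the Innovation Team section (developments, decisions, challenges), without principle-based prompts. The Results section says that data collection began in December 2023, so this applies where still possible.
3. Give each coded segment a date and a prompted or unprompted attribute.
4. Report concordance separately for pre-exposure or unprompted evidence and for post-exposure or prompted evidence. Attribute concordance to spontaneous scaling only where the former supports it.

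The cost is one extra code attribute and somewhat less direct coverage of each principle in the monthly contacts. Steps 3 and 4 remain feasible even if the guide has already been used, provided that segments can be dated.
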